### **\*\*6.2 Efficacy Analysis and Statistical Methods\*\***

Statistical analysis will be performed using R software. For demographic and baseline characteristics, continuous variables conforming to normal distribution will be expressed as mean  $\pm$  standard deviation ( $\bar{x} \pm s$ ) and compared between groups using independent samples t-test; if not normally distributed, they will be expressed as median and interquartile range (IQR) and analyzed using Mann-Whitney U test. Categorical variables will be compared using Chi-square test or Fisher's exact test based on sample size and expected frequencies.

For primary and secondary outcome measures (e.g., FMA-UE, FMA-LE, WMFT, BBS, MBI scores), Linear Mixed Effects Models (LMM) will be used to handle repeated measures data, implemented via the "nlme" package in R, to assess changes over time and differences between groups, accounting for correlations within subjects across multiple time points. Post-hoc subgroup analyses will explore differential efficacy of taVNS across different stroke types (ischemic vs. hemorrhagic) and lesion locations.

For safety indicators, normality tests will first be performed on Heart Rate Variability (HRV) and blood pressure data. If normally distributed, paired sample t-tests will be used to compare values before and during treatment; if not, Wilcoxon signed-rank test will be used. Comparison of adverse event incidence rates between groups will use Chi-square test or Fisher's exact test.  $p < 0.05$  will be considered statistically significant.

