#### **\*\*3.3 Study Groups and Interventions\*\***

To verify the clinical efficacy and safety of bilateral taVNS for stroke motor dysfunction, and its difference compared to unilateral left-sided taVNS, this clinical trial is divided into three groups:

- (1) **\*\*Conventional Treatment Group:\*\*** Based on drug therapy, provide conventional rehabilitation treatment for stroke hemiplegic motor dysfunction, including comprehensive rehabilitation such as exercise therapy, occupational therapy, physical agent therapy, conventional acupuncture, etc.
- (2) **\*\*Left-sided taVNS Group:\*\*** Based on the conventional treatment group, provide classic non-invasive left-sided auricular vagus nerve electrical stimulation. taVNS parameters: left ear, frequency 25Hz, pulse width 300us, current 6 mA.
- (3) **\*\*Bilateral taVNS Group:\*\*** Based on the conventional treatment group, provide non-invasive bilateral auricular vagus nerve electrical stimulation. taVNS parameters: both ears, frequency 25Hz, pulse width 300us, current 6 mA.

**\*\*taVNS Treatment Regimen:\*\*** 30min/session, 2 sessions/day, 6 days/week, for 4 weeks.

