#### **\*\*3.4 Randomization\*\***

##### **\*\*3.4.1 Method for Generating Random Allocation Sequence\*\***

> Use a random number table for randomization.

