## **\*\*6. Statistical Analysis Plan\*\***

### **\*\*6.1 Sample Size Estimation\*\***

Sample size was determined using  $N = 2 \cdot [(Z_{\alpha/2} + Z_{\beta})\sigma/d]^2$  and statistical power analysis software G\*Power 3.1. Referring to the effect size observed in studies like Dawson et al. (Cohen's  $d=0.632$ ), with  $\alpha=0.05$  and statistical power  $(1-\beta)$  equal to 80%, the estimated sample size per group should be 34. Considering a 10% clinical dropout rate, the sample size per group was adjusted to 38, totaling 114 participants across three groups.

\*Reference: Dawson J, et al. Vagus nerve stimulation paired with rehabilitation for upper limb motor function after ischaemic stroke (VNS-REHAB): a randomised, blinded, pivotal, device trial. Lancet. (2021) 397:1545–53.\*

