**\*\*10. Expected Schedule and Completion Date\*\***

This project is expected to be completed in 3 years. The overall schedule and progress are as follows:

[January 2025 - June 2025]{.underline}

Prepare and refine all pre-trial tasks, explain patient inclusion and exclusion criteria, conduct standardized training for scale administration, and provide homogeneous training for taVNS treatment to achieve standardized homogeneity across the three clinical centers. Additionally, complete ethics applications and approvals at the three clinical centers, and complete registration on the Chinese Clinical Trial Registry website.

[July 2025 - June 2026]{.underline}

Begin enrolling stroke patients first in the Rehabilitation Medicine Department of the First Affiliated Hospital of Nanchang University, administer taVNS treatment, monitor safety, and perform assessments including FMA-UE, FMA-LE, WMFT, Balance evaluation and training system, BBS, FAC, MBI, and fNIRS.

[July 2026 - December 2027]

Simultaneously initiate trial enrollment in the Rehabilitation Medicine Departments of The Rehabilitation Hospital Affiliated to Nanchang University and The First Affiliated Hospital of Gannan Medical University, administer taVNS treatment, monitor safety, and perform assessments including FMA-UE, FMA-LE, WMFT, Balance evaluation and training system, BBS, FAC, MBI, and fNIRS.

[December 2027 - June 2028]

Conduct supplementary clinical trials, data collection and processing, statistical analysis of experimental data, manuscript writing, and final reporting.

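### Baseline comparisons name two-group tests for a three-arm trial, and the allocation method names no blocking or centre stratification; both can be fixed at almost no cost, together with stating the baseline- and centre-adjusted model

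*Protocol*

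**What the plan says.** - **Design.** Protocol section 3.3: "this clinical trial is divided into three groups" (conventional treatment, left-sided taVNS, bilateral taVNS). Section 6.1 plans equal arms: "the sample size per group was adjusted to 38, totaling 114 participants across three groups".
- **Baseline tables.** Section 6.2, and the Statistical Analysis row of the synopsis, say that normally distributed baseline variables are "compared between groups using independent samples t-test". Otherwise Mann-Whitney U is used. No omnibus test, choice of pairs or multiplicity rule is given.
- **Allocation.** Section 3.4.1 in full: "Use a random number table for randomization". Section 3.6 repeats this, and section 3.4.2 adds only that randomisation is central. Blocks and strata are not mentioned.
- **Centres.** Section 10 has the lead centre enrolling from July 2025. From July 2026 the other two join: "Simultaneously initiate trial enrollment in the Rehabilitation Medicine Departments".
- **Efficacy model.** Section 6.2 specifies a linear mixed model "to assess changes over time and differences between groups", allowing for within-subject correlation. It names no covariates and does not say whether T0 is a response or a covariate. Section 3.6 collects FMA-UE and FMA-LE at T0, T1 and T2 only, so T2 is the last visit with the primary measures.

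**The concern.** The t-test and the Mann-Whitney test each compare two groups, so the named method does not fit the design. With three arms it must be run as up to three pairwise tests per variable, or on some unstated pair. After proper randomisation any baseline difference is due to chance, so each test examines a null hypothesis already known to be true. A significant result is a false alarm by construction.

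The allocation sequence has to be fixed before the first patient and so belongs in the protocol. With three centres, two of them opening a year after the first, a list without centre strata leaves the mix of arms in each centre to chance. If centres differ in case mix or conventional rehabilitation, a chance imbalance of arms within centre shifts the estimate in that particular trial.

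The baseline FMA score and the centre are known for every patient. Using them in the model costs nothing and can only be relied on if it is written down in advance.

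**Working it through.** **The plan's own figure.** Section 6.1: two-sided α = 0.05, power 80%, d = 0.632, and "the estimated sample size per group should be 34". The stated formula gives 2 × (1.960 + 0.842)² / 0.632² = 39.3, so 40 per group. The figure of 34 is therefore not reproduced. The dropout step is: 34 / 0.9 = 37.8, so 38, and 3 × 38 = 114. The mismatch at 34 is a separate matter; here 34 serves only as the plan's own benchmark for evaluable patients per arm.

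**Baseline tests.** Three pairwise t-tests at 0.05 on one variable, 38 per arm, no true difference (40,000 simulated trials): the chance of at least one significant result is 0.120. If the three tests were independent it would be 1 − 0.95³ = 0.143.

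**Arm sizes if allocation is simple 1:1:1 with 114 patients (assumed).** Each arm has mean 38 and SD √(114 × 1/3 × 2/3) = 5.03. By multinomial simulation:
- chance that some arm is randomised below 34: 0.54
- chance that the largest and smallest arms differ by 10 or more: 0.52
- mean gap between largest and smallest arm: 10.4
- mean variance of a pairwise contrast relative to 38 v 38: 1.018, an increase of about 1.8%
- mean power at d = 0.632 (two-sided z, before dropout): 0.780, against 0.787 with fixed arms of 38

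**Balance within centre.** Centre sizes are not given; 38/38/38 and 60/27/27 are assumed. The figure is the chance of a gap of 6 or more between arms in at least one centre.

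| Allocation | 38/38/38 | 60/27/27 |
|---|---|---|
| Simple | 0.89 | 0.87 |
| Arm totals fixed at 38, no centre strata | 0.67 | 0.60 |
| Permuted blocks of 6 within centre | 0 (largest gap 2) | 0 (largest gap 2) |

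With blocks of 6 within centre the mean overall gap is about 2 (2.1 and 1.8). At a later centre of 30 patients (assumed), simple allocation gives about a 33% chance that one arm is at least twice the size of another.

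**Baseline adjustment.** Let r be the correlation between T0 and T2, not given in the protocol and assumed here. On a unit-SD scale, a change-from-baseline contrast has variance factor 2(1 − r) and a baseline-adjusted contrast 1 − r². The ratio is (1 − r²) / [2(1 − r)] = (1 + r)/2. Power is for 34 per arm, d = 0.632, two-sided z, taking d as the effect divided by the SD at one visit.

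| r (assumed) | Change | Adjusted | Ratio | Power, change to adjusted |
|---|---|---|---|---|
| 0.3 | 1.40 | 0.91 | 0.65 | 0.60 to 0.78 |
| 0.5 | 1.00 | 0.75 | 0.75 | 0.74 to 0.85 |
| 0.7 | 0.60 | 0.51 | 0.85 | 0.92 to 0.95 |
| 0.8 | 0.40 | 0.36 | 0.90 | 0.985 to 0.991 |

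A mixed model that constrains the T0 means to be equal across arms already has this precision, and then the gain is zero.

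**Centre adjustment.** With an assumed centre intraclass correlation of 0.02 to 0.10, the variance factor is 0.98 to 0.90.

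**The case against.** Several stronger readings are tempting, and the document does not support them.

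- **That the baseline tests are how imbalance is handled, or that they trigger adjustment.** Section 6.2 uses them only for demographic and baseline characteristics; efficacy rests on the mixed model. The tests can be computed pairwise. They are ill-matched and pointless, but no efficacy decision is said to hang on them.
- **That allocation is simple or unstratified.** This is inferred from silence. A random number table can generate a blocked or centre-specific list, and section 6.1 plans 38 in each arm. The 54%, 52% and 33% figures hold only if allocation is simple.
- **That unequal arms seriously cost power.** Even under simple allocation the loss is under one percentage point on average.
- **That the staggered start biases the arm comparison.** Patients are randomised to all three arms in each centre and period, so neither centre nor time is systematically tied to arm. Stratifying would not remove the link between centre and calendar time, because that comes from the opening dates.
- **That the model halves the treatment effect by averaging over T0 to T2.** Section 6.2 does not specify such a main effect. Its wording is compatible with an arm-by-visit contrast, and the halving also needs an assumed build-up of effect.
- **That precision is lost by leaving baseline out.** T0 is one of the repeated assessments, and covariates are commonly left to an analysis plan, which is not shown. Their absence is not an error.

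All of this stands, and it limits the point. What it does not answer is that a two-group test is named for three groups, or that the sequence method is silent on blocks and centre in a three-centre trial.

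**Conclusion.** The point holds in a modest form. The one outright misfit is the choice of two-sample tests for three arms, with about a 12% false-flag rate per variable if run pairwise; its consequence is confined to the baseline table. The allocation text is incomplete for a multicentre trial. If allocation is simple, arms will often be visibly unequal, at an average variance cost of about 2%. The larger exposure is imbalance within centre, which under the assumed centre sizes reaches a gap of 6 or more in some centre in 87% to 89% of trials, and in 60% to 67% even if arm totals are held at 38. How far that would move the result depends on differences between centres that the protocol does not give.

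The model statement is not wrong. Stating baseline and centre adjustment is an improvement worth a variance ratio of 0.75 at r = 0.5 or 0.90 at r = 0.8 over a change-type contrast, and nothing if T0 means are already constrained equal. No loss of precision can be sized from the document alone.

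**What to change.** - **Section 3.4.1 (and 3.6):** specify permuted blocks of varying size, stratified by centre, issued through the central randomisation already planned. If such a list is already intended, say so.
- **Section 6.2 and synopsis, baseline:** drop the baseline p values and present descriptive summaries by arm. If a test is kept, use one-way ANOVA or Kruskal-Wallis across the three arms.
- **Section 6.2 and synopsis, efficacy:** state that the mixed model has arm, visit and arm-by-visit terms, adjusts for baseline FMA (or constrains T0 means to be equal) and for centre, and that the arm contrast at T2 is the efficacy estimate.

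The cost is a rewritten allocation list and model statement, with no extra patients, visits or data. The allocation change has to be made before the sequence is used.

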#### **\*\*3.6 Study Procedures\*\***

Study steps mainly include clinical trial randomization and grouping, follow-up and data collection at baseline (T0), at 2 weeks of treatment (T1), at the end of 4 weeks (T2), and at 8 weeks after treatment completion (T3), as detailed below:

- (1) **\*\*Randomization and Grouping:\*\*** Enroll eligible stroke patients with motor dysfunction and assign them to the Conventional Treatment Group, Left-sided taVNS Group, or Bilateral

taVNS Group using a random number table.

(2) **\*\*Collection of Basic Patient History Information:\*\*** Collect basic information for enrolled subjects, including age, gender, time since onset, stroke type, education level, marital status, etc.

(3) **\*\*Data Collection at T0, T1, T2 time points:\*\*** Fugl-Meyer Assessment for Upper Extremity (FMA-UE) and Lower Extremity (FMA-LE), Wolf Motor Function Test (WMFT), Balance evaluation and training system, Berg Balance Scale (BBS), Holden Functional Ambulation Classification (FAC), Modified Barthel Index (MBI), functional Near-Infrared Spectroscopy (fNIRS).

(4) **\*\*Data Collection at T3 follow-up time point:\*\*** Follow up via phone or outpatient visit to collect Berg Balance Scale (BBS) and Modified Barthel Index (MBI) scores at 8 weeks after treatment completion.

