### **\*\*3.8 Endpoint Evaluation Measures\*\***

#### **\*\*3.8.1 Primary Endpoint Evaluation Measures\*\***

- > (1) Fugl-Meyer Assessment for Upper Extremity (FMA-UE)
- > (2) Fugl-Meyer Assessment for Lower Extremity (FMA-LE)

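### Two unranked primary endpoints, three arms and two post-baseline visits share one unadjusted 0.05 threshold, and no primary contrast, visit or either/both rule is named

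*Protocol*

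**What the plan says.** Section 3.8.1 (and the synopsis) lists two primary measures, FMA-UE and "Fugl-Meyer Assessment for Lower Extremity (FMA-LE"), with no order between them and no statement of whether success on one is enough.

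Section 3.3 defines three arms: conventional, left-sided taVNS and bilateral taVNS. It gives two comparative purposes: whether bilateral stimulation works, and how it differs from left-sided stimulation.

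Section 3.6 schedules assessments "at 2 weeks of treatment (T1), at the end of 4 weeks (T2"), plus a T3 follow-up. T3 collects only BBS and MBI, so FMA has exactly two post-baseline visits.

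Section 6.2 fits a linear mixed model "to assess changes over time and differences between groups". The only decision rule is that p below 0.05 "will be considered statistically significant". No contrast, visit or adjustment is singled out.

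Section 6.1 uses a two-group formula with undivided alpha 0.05 and reports power "equal to 80%, the estimated sample size per group should be 34", raised to 38 for dropout.

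**The concern.** A confirmatory trial needs to say in advance which result decides it. Here several results could: either scale, any of up to three pairwise comparisons, and either visit. Each would be judged at 0.05 on its own. The sample size assumes one test at 0.05, but the analysis section does not restrict the primary claim to one test.

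As written, a single nominal p below 0.05 (for example FMA-LE at T1 in one comparison) could be reported as a positive primary result without breaching the protocol. That matters because section 11 plans a clinical application protocol for bilateral taVNS, at least three demonstration units and promotion across the province.

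**Working it through.** **Inputs from the protocol.** Two primary endpoints (3.8.1); three equal arms (3.3, 6.1); two post-baseline FMA visits (3.6); threshold 0.05 (6.2); two-sided alpha 0.05, power 80%, d = 0.632, 34 per arm (6.1).

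**Assumed inputs.** Correlation between the two FMA scales: 0 to 0.9. Correlation between T1 and T2: 0.5 to 0.9. The protocol gives neither.

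**The plan's own figure.** The printed formula is n = 2[(1.960 + 0.842)/0.632]². Here 2.802/0.632 = 4.433, its square is 19.65, and twice that is 39.3, so 40 per arm. The stated 34 does not follow from it. The dropout step does: 34/0.9 = 37.8, so 38. The shortfall is a separate matter, but it sets the power quoted below. The formula is for one comparison of two groups and contains no allowance for several tests.

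**Simple bound.** With k independent tests the familywise error is 1 − 0.95^k. For k = 2 this is 1 − 0.9025 = 9.75%; for k = 12 it is 46%. The second value cannot be reached, because pairwise contrasts share arms.

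**Simulation with shared arms.** All arms were given the same true mean, each test was two-sided at 5% on a normal statistic, and 300,000 to 400,000 runs were made per setting. The error counted is at least one p below 0.05 on either endpoint.

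| Tests that count as primary | Number | Familywise error |
|---|---|---|
| One omnibus group test per endpoint | 2 | 7% to 10% |
| One contrast, one visit | 2 | 7% to 10% |
| Two bilateral contrasts, one visit | 4 | 13% to 17% |
| Three contrasts, one visit | 6 | 17% to 23% |
| Two bilateral contrasts, both visits | 8 | 17% to 30% |
| Three contrasts, both visits | 12 | 22% to 38% |

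In each row the low end has endpoint correlation 0.9 and the high end 0; in the last two rows the visit correlation is 0.9 and 0.5 respectively. For all 12 tests, intermediate pairs (endpoint/visit) give 33% at 0.5/0.7, 29% at 0.7/0.8 and 25% at 0.8/0.9. Outside the stated grid, 0/0 gives 41% and 0.9/0.95 gives 21%.

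**Favourable direction only.** Counting only errors that favour the more active arm gives about 4% to 5% for one contrast at one visit, 6% to 9% for two bilateral contrasts at one visit and 9% to 13% for three. For all 12 tests it is 14% at 0.8/0.9 and 22% at 0/0.5. The matching nominal level is 2.5%, not 5%.

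**If both endpoints must succeed** on one named contrast at one named visit, the error is at most 5%. The protocol does not state this rule.

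**Power at 34 per arm, d = 0.632 (two-sample t-test).** At 0.05: 73%. At 0.05/6: 46%. Requiring both endpoints, with d = 0.632 true for each: between 0.728² = 53% (uncorrelated) and 73% (perfectly correlated).

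**The case against.** The strongest reply is that the protocol nowhere says every contrast is tested at every visit. A mixed model can yield one omnibus group or group-by-time test per endpoint, and that fits section 6.2 equally well. Section 3.3 states two questions, not three; left-sided versus conventional is never given as an efficacy comparison. A reader might infer that 12 primary tests are planned and that the chance of a false primary claim is therefore 20% to 30%. The document does not support that: the list of tests is not fixed, and the percentage depends on which tests count and on correlations it does not give. This part of the objection stands.

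It is also fair that two-sided counts include results against taVNS, so they overstate the risk of a false favourable claim by roughly a factor of two.

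Finally, contrasts and testing order are often left to a separate analysis plan. That carries less weight here. Section 6 is itself headed as the statistical analysis plan, states the decision rule and has already spent the whole alpha of 0.05 on one comparison. Naming two unranked primaries under that rule is a defect in what is written, not just a missing detail.

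**Conclusion.** The point holds in a bounded form. Under the stated rule, if either endpoint suffices, type I error for the primary claim is not held at the 0.05 used in section 6.1. It is about 7% to 10% on the narrowest such reading and about 22% to 38% if all contrasts at both visits count. The range is wide because nothing in the protocol says which test decides the trial.

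The existence of the inflation is certain on an either-endpoint reading. Its size is not: it rests on assumed correlations and on which tests are run. No single percentage should be quoted as the trial's error rate.

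**What to change.** In 6.2, define the primary estimate as the between-arm difference at T2 from the mixed model, and prespecify one rule that controls alpha before any data are seen.

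One option is a fixed sequence at two-sided 0.05, stopping at the first failure:

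1. bilateral versus conventional, FMA-UE;
2. bilateral versus conventional, FMA-LE;
3. bilateral versus left-sided, FMA-UE;
4. bilateral versus left-sided, FMA-LE.

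The order is the sponsor's choice. Nothing in the protocol ranks FMA-UE above FMA-LE, although the sample size reference is an upper-limb trial. Requiring both endpoints, or a Holm procedure, would also serve. Report left-sided versus conventional, T1 and the secondary endpoints as estimates with 95% confidence intervals and no confirmatory claim. Section 6.1 should name the contrast and endpoint that the sample size is for.

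The cost is one paragraph, and the fixed sequence needs no extra patients to keep full alpha for its first test. The downside is that later contrasts cannot be claimed once an earlier one fails. With first-step power about 73% at 34 per arm and d = 0.632, the bilateral versus left-sided question would often not be reached if placed last. An equal split over six tests would cost more, at 46% power per test.

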### **\*\*6.3 Analysis Populations\*\***

Subjects who do not comply with the study protocol will be excluded from the analysis.

## **\*\*7. Research Related Ethics\*\***

### **\*\*7.1 Ethics Committee Review\*\***

> This protocol, the written informed consent form, and any materials directly related to subjects must be submitted to the Ethics Committee. The study may only formally commence after obtaining written approval from the Ethics Committee. The investigator must submit an annual study report to the Ethics Committee at least once a year. Upon study termination and/or completion, the investigator must notify the Ethics Committee in writing; the investigator must promptly report all changes occurring during the research work (such as revisions to the protocol and/or informed consent form) to the Ethics Committee and must not implement new modifications arbitrarily without prior approval from the Ethics Committee, unless changes are necessary to eliminate an apparent and immediate risk to subjects. In such cases, the Ethics Committee will be notified.

